**Figure 1 F1:**
[figure not shown]
**Example of a logic tree representing the Boolean expression “*****more than 50 common naevi*****V [*****skin type IV*****Λ (*****MC1R R151C*****V*****brown hair*****)]”.**

The searching for the optimum combinations of *MC1R* variants and phenotypic characteristics mostly associated with skin cancer will be undertaken by a (stochastic) simulated annealing algorithm [104-106]. This algorithm has a good chance to find a model that has the best or close to best possible score but, in the presence of noise in the data, typically overfits data. In order to select the best model, application of a combination of cross-validation and randomization tests has been suggested [104,105].

In an explanatory setting, at risk gene-phenotype combinations will be identified among a very large number of possible combinations by logic regression-based methods recently proposed [106,107]. The skin cancer risk of the identified subpopulations will be estimated within the pooled-analysis context using the two-stage analysis previously described.

Structural equation models will be also applied to eventually clarify the independent and dependent role of *MC1R* variants on skin cancer by phenotypic characteristics.

Finally, the role of environmental exposure will be investigated by entering new covariates in the models, by subgroup analyses and by studying gene-environment and phenotype-environment interactions using traditional and new proposed methodologies [108].

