## Brief description of the collected data and statistical power

The final dataset was created in June 2011 and included data on 7,806 melanoma cases, 3,151 NMSC cases (2,211 BCC, 788 SCC and 152 with both), and 14,875 controls.

Distribution of data according to study country in which the study was performed is presented in Table 2. The majority of data came from Europe, especially from southern European populations. There was no significant difference in participation rate according to study area (Fisher exact test p-value: 0.25).

**Table 2 T2:** Summary of data included in the M-SKIP project by geographical location

**Study area**	**Invited investigators**	**Participant investigators (studies)**	**Melanoma cases**	**NMSC cases**	**Controls**
Africa	1	0 (0)	0	0	0
Asia	3	2 (2)	0	0	345
Australia	4	2 (3)	744	298	290
Northern Europe^a^	8	6 (6)	858	1629	8095
Central Europe^b^	6	3 (4)	977	639	2398
Southern Europe^c^	9	8 (12)	2,747	0	2263
North America	13	11 (12)	2,480	585	1484
**TOTAL**	**43**^**d**^	**31**^**d**^**(39)**	**7808**	**3151**	**14875**

*NMSC* = non melanoma skin cancer.

^a^ includes Denmark, Norway, Sweden, The Netherlands, UK.

^b^ includes France, Germany, Poland.

^c^ includes Greece, Italy, Spain.

^d^ one investigator collected data for two different areas (North America and Asia).

The main characteristics of the studies included in the M-SKIP database are described in Table 3. The majority are case–control studies (54%) with population or healthy controls and case–control matching. Phenotypic characteristics were frequently assessed by self-administered questionnaire (41%) or examination by a dermatologist or research nurse (36%). The majority of studies sequenced the entire coding region of the *MC1R* (67%) and used blood as DNA source (62%).

**Table 3 T3:** Main characteristics of the included studies

	**Studies (%) N = 39**	**Melanoma cases (%) n = 7806**	**NMSC cases (%) n = 3151**	**Controls (%) n = 14875**

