### Two-stage analysis with random effects models

The two-stage analysis method [100] will allow us to overcome the problem of the availability of different study covariates. The pooled-estimates of the association of *MC1R* variants with each skin cancer type and each phenotypic characteristic will be calculated as follows.

First, study-specific ORs will be calculated by applying logistic regression to the data from each study to estimate the odds of skin cancer conditional on the presence of a *MC1R* variant (*X*), controlling for confounders *Z*_*k*_. For study *k* (*k = 1,…,K*), assuming just one confounder, the model is written as:

(4)$$\text{logit}(\pi_{\mathrm{ik}}/X)=\alpha_{k}+\beta_{k}X_{\mathrm{ik}}+\gamma_{k}Z_{\mathrm{ik}}$$

where *π*_*ik*_ is the conditional probability of skin cancer for subject *i* (*i = 1,…,n*_*k*_) of study *k*. Although *MC1R* variants were uniformly defined across studies, the confounders *Z*_*k*_ may be specific to a particular study. Analyses with original covariates and with recoded data will be performed and compared. The exposure log-odds ratio for study *k* is denoted *β*_*k*_, the confounding log-odds ratio is denoted *γ*_*k*_, and the *α*_*k*_ are the study-specific intercepts. The *β*_*k*_ are assumed to vary across studies according to the second-stage model:

(5)$$\beta_{k}=\beta +b_{k}+e_{k}$$

where *β* is the pooled-exposure log-odds ratio, *b*_*k*_ are random effects with *b*_k_ ~ N(0, *σ*^*2*^_*b*_), where *σ*^*2*^_*b*_ represents the variability of the study-specific exposure effects *β*_*k*_ about the population mean *β,* and *e*_*k*_ are independent errors with *e*_k_ ~ N(0, *σ*^*2*^_*k*_), where *σ*^*2*^_*k*_ describes the within-study variation of the *β*_*k*_. In the first stage ${\hat{\beta }}_{k}$and its variance ${\hat{\sigma }}_{k}^{2}$ are estimated from equation 4, separately for each study.

The two-stage estimator of the pooled exposure effect *β* is a weighted average of the ${\hat{\beta }}_{k}$, weighted by the inverse marginal variances of the ${\hat{\beta }}_{k}$, denoted $w_{k}={\left({\hat{\sigma }}_{k}^{2}+\sigma_{b}{}^{2}\right)}^{-1}$. Thus:

(6)$$\hat{\beta }=(\sum_{k}w_{k}{\hat{\beta }}_{k})/\sum_{k}w_{k}$$

(7)$$\mathrm{var}(\hat{\beta })={\left(\sum_{k}w_{k}\right)}^{-1}$$

Two methods [100] are frequently used to estimate the random effects variance *σ*^*2*^_*b*_ in equations 6 and 7. These methods are pseudo-maximum likelihood and moment estimation.

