### Joint association of MC1R and phenotypic characteristics with skin cancer risk

Stratified analysis for the association of *MC1R* variants with each skin cancer type will be performed for different phenotypic characteristics. The hypothesis of homogeneity of ORs among strata will be verified using the Breslow-Day test [102].

In order to identify combinations of *MC1R* variants and phenotypic characteristics associated with each skin cancer type, we will perform logic regression, a recently proposed tree-based statistical method intended for binary predictors [103]. This approach is particularly useful for detecting subpopulations at high or low risk of disease, characterized by high-order interactions among covariates, and thus the methodology could be well applied to the study of complex diseases like cancer. First, we will dichotomize continuous and categorical variables by choosing appropriate thresholds and by creation of dummy variables. For phenotypic characteristics we will define dummy variables in order to 1) have as much differentiation as possible in hair and eye color, and 2) separate the extreme classes of skin type and common nevi count from intermediate classes, because it has been suggested [21] that in the meta- and pooled-analysis setting misclassification affects the intermediate classes of exposure more than the extreme ones. Let *X*_*1*_*, X*_*2*_*,…, X*_*p*_ be the binary predictors obtained by dichotomization, and let *Y* be the binary response variable (case/control status). The appropriate logic regression model can be written as:

(8)$$\text{logit}(Y=1|X_{1},X_{2},\ldots ,X_{n})=\alpha +\sum_{j=1}^{k}\beta_{j}L_{j}$$

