where *L*_*j*_ is a Boolean expression of the predictors *X*_*i*_, such as $L_{j}=X_{4}^{C}\wedge (X_{5}\vee X_{1}\vee X_{3}^{C})$ with ∧=AND, ∨=OR and ${}^{C}=\text{NOT}$. Logic regression could be generally applied to any type of regression outcome as long as the proper scoring function is specified. For the logic regression model in equation 8, the goal is to find the Boolean expressions *L*_*j*_ that minimize the binomial deviance, with the parameters *β*_*j*_ and the Boolean expressions *L*_*j*_ estimated simultaneously. The output from logic regression is represented as a series of trees, one for each Boolean predictor *L*_*j*_, and the associated regression coefficient. An example of a logic tree that may be applied to our pooled analysis is shown in Figure 1. Using this representation it is possible to start from a logic tree and obtain any other logic tree by a finite number of operations such as growing of branches, pruning of branches, changing of predictors and/or operators.

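### Gene-phenotype combinations picked by an outcome-driven logic regression search get two-stage odds ratios with no hold-out or selection correction described, so estimates for weak signals and small outcomes would be inflated

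*Protocol article*

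**What the plan says.** All of this is in the Protocol article. The section on the joint association of MC1R and phenotype introduces logic regression to find risk groups "characterized by high-order interactions among covariates". The search minimises binomial deviance on case/control status, with the Boolean terms and their coefficients "estimated simultaneously". The text after Figure 1 says that the annealing search, "in the presence of noise in the data, typically overfits data". On a safeguard it says: "In order to select the best model, application of a combination of cross-validation and randomization tests has been suggested".

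Combinations are then to be picked out "among a very large number of possible combinations by logic regression-based methods recently proposed", and the next sentence sets the estimation step: "The skin cancer risk of the identified subpopulations will be estimated within the pooled-analysis context using the two-stage analysis previously described".

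That two-stage analysis (equations 4 to 7) weights study estimates by 1/(within-study variance + between-study variance) and takes the variance of the pooled estimate as the inverse of the summed weights. The section describing the collected data reports one final dataset, which "included data on 7,806 melanoma cases, 3,151 NMSC cases (2,211 BCC, 788 SCC and 152 with both), and 14,875 controls".

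**The concern.** A combination is retained because it separates cases from controls well in the data searched. If its OR is then estimated in those data, the chance part of that separation is counted as effect. The OR moves away from 1, and the nominal interval is centred in the wrong place and ignores the search. Equation 7 carries within-study and between-study variation only, so it cannot absorb this. Cross-validation and randomization tests, even if run, help decide which model to keep. They do not correct the OR or interval of the model kept.

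At stake are the risks reported for particular gene-phenotype subgroups. The plan intends this for each skin cancer type, so it includes outcomes with few cases.

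**Working it through.** **The plan's own figures.** The article gives no figure for this step. Its nearest reproducible figure is the main-effect sample size for OR 1.5 at 90% power. With two-sided alpha 0.05 (assumed), continuity correction and the mid-point allele frequencies, 1.5% gives 7,428 per group (stated: about 7,500) and 9% gives 1,384 (stated: 1,400). The concern does not depend on this. It shows only that 1.5 is an effect size the authors regard as realistic.

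**Inputs from the article.**
- Melanoma in case-control studies: 5,092 cases and 6,852 controls (Table 3).
- Squamous cell carcinoma (SCC) only: 788 cases. Setting them against 6,852 controls is a generous pairing.
- Subjects with common nevi data: 3,817 melanoma cases, 442 NMSC cases and 1,181 controls (Table 1). The plan makes nevi count a logic-regression predictor, and its example tree uses it. A complete-case search that includes nevi therefore has at most these numbers.

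**Assumed.** Independent binary predictors, their frequencies and the depth of search.

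**Method.** Simulate cases and controls, search for the best Boolean set, and estimate its OR in the same data. From the 2x2 table, log OR = log(ad/bc), SE = sqrt(1/a + 1/b + 1/c + 1/d) and the interval is log OR ± 1.96 SE. Compare with the true OR of the same selected set, taken from a much larger fresh sample.

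**Set-up A:** 18 predictors, prevalence 3-40%, up to 3 leaves, two predictors with a true effect.

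| Cases vs controls | True OR of each predictor | Same-data OR | True OR of selected set | Ratio | Coverage |
|---|---|---|---|---|---|
| 5,092 vs 6,852 | 1.3 | 1.36 | 1.34 | 1.01 | 92% |
| 3,817 vs 1,181 | 1.3 | 1.42 | 1.30 | 1.09 | 59% |
| 3,817 vs 1,181 | 1.5 | 1.61 | 1.54 | 1.05 | 92% |
| 788 vs 6,852 | 1.3 | 1.51 | 1.29 | 1.17 | 47% |
| 442 vs 1,181 | 1.3 | 1.78 | 1.23 | 1.45 | 15% |
| 442 vs 1,181 | 1.5 | 1.85 | 1.45 | 1.28 | 43% |

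The rows at 3,817 and the last row rest on 150 runs each, so their coverage has a standard error of at most sqrt(0.25/150) = 4 percentage points. In the rows at 5,092, 788 and 442 with true ORs of 1.3, split-sample estimation covered 93-97%.

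**Set-up B:** 19 predictors (9 variants, 10 phenotype dummies), greedy AND/OR tree of up to 6 leaves, over 5,000 runs per row. Ratios are medians of per-run ratios, so they need not equal the quotient of the two median ORs.

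| Cases vs controls | Truth | Same-data OR | True OR | Ratio | Coverage |
|---|---|---|---|---|---|
| 5,092 vs 6,852 | no effect | 1.36 | 1.00 | 1.36 | 0.00 |
| 5,092 vs 6,852 | one OR 1.5 | 1.54 | 1.52 | 1.02 | 0.93 |
| 5,092 vs 6,852 | several | 2.02 | 1.95 | 1.03 | 0.90 |
| 788 vs 6,852 | no effect | 1.68 | 1.00 | 1.68 | 0.00 |
| 788 vs 6,852 | one OR 1.5 | 1.80 | 1.44 | 1.28 | 0.35 |
| 788 vs 6,852 | several | 2.15 | 1.93 | 1.11 | 0.76 |

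Searching in one half and estimating in the other gave coverage of 0.95 in all six rows, with estimate/true ratios of 0.98 to 1.01.

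**Does two-stage pooling help?** At 5,092 vs 6,852, an exhaustive search over sets of up to 3 literals with no true effect gave 1.47 from the pooled table and 1.45 from a 21-study random-effects model. Coverage was 0.00 for both, so pooling does not remove the bias. The same 21-study run at 788 cases is not used as evidence: there even fresh-data estimates were off (1.49 against 1.00), so something other than selection, probably very small cells within studies, was also at work.

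**The case against.** **The article never says that the same subjects serve both steps.** This is correct. A reader might take same-subject estimation as stated, but it is an inference from there being one dataset and no described split. The cited search methods are not at hand, and a fuller plan could hold a discovery/estimation split. Against that, the Background presents this part as the analysis plan to be applied, and the text does fix the sequence of search then two-stage estimate.

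**The no-effect rows are a worst case.** This also stands. They always report the best set found, whereas a randomization test, if run, would screen out most pure-noise combinations. A complete absence of effect is also implausible for melanoma, where the rationale section cites associations for five variants. Such screening would still leave the ORs of retained combinations uncorrected.

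**For melanoma at full size the harm is slight.** This stands too. The tables show it, and it limits the conclusion.

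**The setting is called explanatory.** That lowers the stakes but does not remove the issue: the combinations still receive an OR from the plan's main estimator, with no caveat attached to the estimate.

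**Conclusion.** The point holds in a bounded form. As written, the plan would give ORs too far from 1 and intervals that under-cover for combinations chosen by the search. The effect is serious for weak signals, for NMSC and SCC, and for searches that include sparsely recorded covariates. It is small for melanoma at full size with real effects: about 1-4% inflation and coverage about 0.90-0.93. The sizes rest on assumed predictor frequencies, independence and search depth, and on same-data estimation. The direction was the same in every scenario run.

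Three stronger readings are not supported:
- That the intervals fail to cover in general. Coverage ranged from near nominal to very poor.
- That these subgroup risks are the main output of the third aim. That aim also covers stratified and interaction analyses, which do not depend on the search.
- That larger trees always make it worse. With no true effect, the 6-leaf greedy search gave less inflation than the 3-literal exhaustive search (1.36 against 1.47, and 1.68 against 1.76). Those searches also differ in kind.

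The step should be corrected before logic-regression risks are reported. It does not touch the single-variant or stratified results.

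**What to change.** Label every same-data two-stage OR of a selected combination as apparent and exploratory. Beside it, report a selection-corrected estimate that repeats the whole search within each resample.

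- **Melanoma:** select combinations in one set of studies, fix them, and estimate them in the remaining studies with equations 6 and 7.
- **NMSC and SCC:** a hard split of studies is costly. One cohort holds 1,099 of the 3,151 NMSC cases (35%, Table 3), and Southern Europe contributes none (Table 2). Use study-level cross-validation or a bootstrap optimism correction instead. Where the selected combination differs between folds, describe the result as the performance of the selection procedure, because pooling held-out estimates does not then give the OR of any single combination.

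The plan should also commit to the cross-validation and randomization tests that it now only mentions as suggested.

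The cost is programming time and wider intervals. If half the total weight is in the estimation set, equation 7 doubles the variance, so the standard error grows by sqrt(2) = 1.41. No new data are needed.

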### Use of MC1R data

In all the proposed analyses, each of the nine most frequently investigated *MC1R* variants (V60L, D84E, V92M, R142H, R151C, I155T, R160W, R163Q, D294H), as well as known rare mutations affecting *MC1R* function [109] will be evaluated assuming different inheritance models and choosing the one that fits the data best. Haplotype frequencies will be estimated using the iterative Expectation-Maximization algorithm [110,111], and their association with each skin cancer type and phenotypic characteristics will be evaluated. Moreover, for the studies that sequenced the entire gene, we will evaluate the impact on skin cancer and phenotypic characteristics of the total number of *MC1R* variant alleles and of the scores obtained from appropriate classification of *MC1R* variants [112].

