**DNA source**				
Blood	24 (62%)	4645 (60%)	2743 (87%)	13304 (89%)
Buccal cells	14 (36%)	3161 (40%)	408 (13%)	1326 (9%)
Tissue	1 (3%)	0	0	245 (2%)

*NMSC* = non melanoma skin cancer.

^a^ healthy subjects are blood donors, friends or relatives of cases.

^b^ individual or frequency.

^c^ includes RFLP, SNaPshot, allele discrimination assay.

We calculated that the minimum required sample size to find a statistically significant association between a *MC1R* variant and melanoma assuming a similar association to that observed in our previous meta-analysis [14] (Odds Ratio (OR) = 1.5) is around 7,500 cases and 7,500 controls for rare variants (1-2% allele frequency in controls), and 1,400 cases and 1,400 controls for common variants (8-10% allele frequency in controls), with 90% statistical power. Sample size for gene-environment interaction analysis was also calculated with the program POWER, version 3.0 [96]. Considering the study of a simple two-way interaction between an environmental factor and a rare *MC1R* variant, around 5,000 cases and 5,000 controls would be needed to observe a multiplicative interaction effect of 2.0, arising to 16,000 cases and 16,000 controls to observe a smaller multiplicative effect of 1.5, both with 90% statistical power. For common *MC1R* variants, the same gene-environment interaction effects of 2.0 and 1.5 could be observed with around 1,200 cases and 1,200 controls, and with around 3,500 cases and 3,500 controls, respectively. Our sample size therefore is appropriate for the purpose of the analysis, and large enough to allow stratified and interaction analyses, especially to find even small interaction effects with the most frequent variants, and larger interaction effects for less common variants.

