### Combining data into a single dataset with random effects models

A first analysis using data combined into one dataset, is to fit them with logistic regression models with random slope. Considering a dominant model, let *π*_*ik*_*/X* be the probability of skin cancer for subject *i* (*i = 1,…,n*_*k*_) of study *k* (*k = 1,…,K*) conditional on the presence of a certain *MC1R* variant (*X*). We will account for the fixed *MC1R* effect and the random selection of studies, assuming a model that relates *MC1R* and study effects linearly to the logit of the probabilities:

(3)$$\text{logit}(\pi_{\mathrm{ik}}\text{/ }X)=\alpha +\beta X_{\mathrm{ik}}+b_{k}X_{\mathrm{ik}}$$

In this model the transformed regression coefficient exp(*β*) is the odds of skin cancer for a subject with the *MC1R* variant compared with a subject without the *MC1R* variant, and the *b*_k_ are the study-specific coefficients accounting for the random selection of studies, with *b*_k_ ~ N(0, *σ*^*2*^_*b*_), where *σ*^*2*^_*b*_ represents the between study variance of the *MC1R* effect.

The logistic regression model above described could be applied to different inheritance models and could include covariates, in order to adjust the studied associations by possible confounding factors. In order to include the available information from all the studies, missing values could be estimated in the model with multiple imputation and/or the creation of a missing-data indicator variable. However, when the majority of missing data are the results of non-availability of certain variables in some studies, as for the M-SKIP project, the use of both multiple imputation and the missing-data indicator would be likely to introduce a bias in comparison with the complete case method [98,99] and a two-stage approach would be preferred.

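### Picking each variant's inheritance model by best fit on the analysis data, with no allowance described for the choice, can raise the per-variant false-positive rate

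*Protocol article*

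**What the plan says.** The rule is in the Protocol article, section on use of MC1R data. For nine named variants and the known rare functional mutations, in all the proposed analyses, each "will be evaluated assuming different inheritance models and choosing the one that fits the data best".

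The only inheritance model named is in the section on combining data with random-effects models. Equation 3 is introduced with "Considering a dominant model", and the same section adds that the model "could be applied to different inheritance models and could include covariates". For M-SKIP the article then prefers the two-stage method: a logistic regression in each study, followed by random-effects pooling.

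The power paragraph, in the section describing the collected data, takes "Odds Ratio (OR) = 1.5". Where the allele is frequent, its requirement reads "1,400 cases and 1,400 controls for common variants (8-10% allele frequency in controls), with 90% statistical power". Where the frequency is only 1-2%, the stated need rises to about 7,500 in each group.

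Cross-validation and randomization tests are mentioned as a guard against overfitting, but only for the logic regression search.

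**The concern.** Fitting several codings of one genotype and keeping the best gives a variant more than one chance to look associated. If the retained model is then read against the usual threshold, as though it had been the only one fitted, its p-value is too small. This is a procedure that the article states, and it is stated for every analysis. The article recognises the same hazard for logic regression, where it says a search of this kind tends to overfit, but it applies no comparable protection here.

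At stake is how far a claimed association of a single common variant with a skin cancer or a pigmentation trait can be trusted.

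**Working it through.** **1. The plan's own sample sizes.** Inputs from the article: OR 1.5, power 90%, mid-range frequencies 9% and 1.5%. Two-sided alpha 0.05 is assumed, because no level is stated. With p1 = OR·p0/(1 − p0 + OR·p0) and p̄ the mean of p0 and p1,

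n = [1.96·√(2p̄(1−p̄)) + 1.282·√(p0(1−p0) + p1(1−p1))]² / (p1−p0)²,

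and with continuity correction n_cc = (n/4)·[1 + √(1 + 4/(n(p1−p0)))]².

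- p0 = 0.09: p1 = 0.135/1.045 = 0.129; n = 1,334; n_cc = 1,384 (article: 1,400).
- p0 = 0.015: p1 = 0.0225/1.0075 = 0.0223; n = 7,158; n_cc = 7,428 (article: 7,500).

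The stated sizes fit one binary exposure, tested once at two-sided 5%, with the allele frequency used as exposure prevalence. Using the dominant carrier prevalence 1 − (1−q)² instead gives 795 and 3,685 (no continuity correction), which do not match. There is no sign of an allowance for a model search.

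**2. How far the codings overlap.** Under Hardy-Weinberg proportions and no association, the test statistics at allele frequency q have these correlations:

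- dominant-additive: √(2(1−q)/(2−q)) = √(1.82/1.91) = 0.98 at q = 0.09
- additive-recessive: √(2q/(1+q)) = √(0.18/1.09) = 0.41
- dominant-recessive: √(q(1−q)/((2−q)(1+q))) = √(0.0819/2.0819) = 0.20

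Dominant and additive are nearly one test. Recessive is close to a second one, so the candidate set drives the result.

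**3. One combined dataset** (7,806 melanoma cases, 14,875 controls; null simulation, nominal 5%, 8-10% allele frequency):

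| Rule | Rejection rate |
|---|---|
| Any single model | 4.9-5.2% |
| Best of dominant and additive | 5.9-6.1% |
| Best of dominant, additive and recessive | 10.2-10.4% (normal limit 10.3%) |

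At 1-2% frequency, dominant and additive together give 5.3-5.5%. Adding recessive gives anything from 5.3% to 12.7% depending on the test, because homozygotes are few.

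**4. The preferred two-stage analysis.** Assumed: 17 studies of about 300 cases and 400 controls, moment estimator, 8-10% frequency. The article's 21 case-control studies, with 5,092 melanoma cases and 6,852 controls, guide the study sizes but do not fix them. A study then has about 700 × 0.09² = 5.7 homozygotes, so recessive estimates are sparse.

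Without true heterogeneity:

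- Single dominant or additive model: 3.7-4.1%.
- Largest |Z| of dominant and additive: 4.5-4.9%.
- Largest |Z| of three: 5.9-6.9% when studies with empty homozygote cells are dropped or given a half-count correction, about 1.6-1.7 times the single model. A second simulation gave 8.5% against 4.1%, a ratio of 8.5/4.1 = 2.1. How the sparse studies are handled accounts for a gap of this size.
- Model with the best summed study deviance: 3.4-4.1%, so no inflation. This criterion rewards study-to-study noise: it chose the recessive model in about 57-63% of null datasets, and that model's pooled test is conservative.

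With an assumed between-study SD of 0.2 in the log-OR, two simulations gave 11.1% against 6.6%, and 12.6% against 6.9-7.0%, for best of three against a single model. That is 1.7-1.8 times. Part of the excess over 5% here belongs to the random-effects test itself and not to the selection.

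**The case against.** The strongest reply is that the size of the effect rests on things the article does not state: which models compete, what best fit means, the significance level, and what is tested after selection. A condensed journal article may leave these to a fuller plan. In the preferred two-stage analysis one reasonable criterion gives no inflation, and without heterogeneity the moment estimator keeps single-model rates below 5%. All of this stands, and it rules out a single figure. It does not remove the point, because selecting on the analysis data is a stated rule.

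A reader might also infer more than the documents support:

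- That selection simply doubles the error rate. This holds for common variants in one combined dataset with a recessive candidate tested at 5%, and not in general.
- That nine variants against three cancers and eight phenotypes (99 tests) would give about 10 false positives in place of 5. That needs every association to be null and every variant common. The article cites earlier associations for several of these variants and plans explicitly for rare ones.
- That one variant will be dominant for one cancer and recessive for another. The text does not say whether the choice is made separately by outcome.
- That the selected odds ratios are biased away from the null. Only rejection rates were calculated.
- That the dominant coding in equation 3 contradicts the later rule. It introduces an illustrative equation, and the same section allows other models.

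**Conclusion.** The concern holds in conditional form. The plan selects the inheritance model on the analysis data and describes no allowance for doing so. With a two-sided 5% test after selection, the per-variant error for a common variant in one combined dataset is about 6% (dominant and additive) to about 10% (recessive added). In the two-stage analysis it lies between no inflation and about 1.6-2 times the single-model rate. These figures assume the 5% level, the candidate sets shown, Hardy-Weinberg proportions and, for the two-stage results, the study sizes in the working. The direction and the remedy do not depend on the exact figure. This is worth correcting before analysis, but it does not undermine the project.

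**What to change.** State one primary inheritance model in advance for all variants and outcomes: either the dominant coding already written in equation 3 or a per-allele coding. Report the other models as sensitivity analyses. In the combined-dataset simulation any single pre-specified model brings the rate back to 4.9-5.2%.

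If best-fit selection is kept, list the candidate models and the fit criterion, and base the p-value on the maximum statistic over the candidates, permuting case status within study (for phenotype analyses, the phenotype). As a guide, with three candidates at 8-10% frequency the normal-limit critical |z| is about 2.26-2.27 instead of 1.96.

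The first option costs one sentence and some power if a variant is truly recessive; that loss was not quantified. The second costs computing time and a stricter threshold.
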